## Secondary outcome analysis

Secondary outcomes will be analysed using similar models to those described for the primary outcome.

## Fidelity analysis

We will audio-record one randomly selected group intervention session from each cohort to assess facilitator fidelity to the manual using a standard checklist which we have developed. We will report session attendance. We will report adherence as the proportion of participants who have attended (or had a catch-up for) at least five main sessions (moderate attendance) as well as those attending or catching-up all ten main sessions. We will also report the number of main sessions (or catch-ups) attended, using appropriate summary statistics, and the relationship between number of sessions attended and treatment effect (measured on the primary outcome) in the intervention arm.

## Economic evaluation

The economic analysis will evaluate the cost-effectiveness of the APPLE Tree intervention compared to the control over 24 months from an English NHS and Personal Social Services (PSS) perspective, using patient-level trial data. The principal analysis will be the incremental cost per quality-adjusted life year (QALY) gained with the APPLE Tree intervention compared to the control from a health and social care cost perspective. A secondary analysis will report the incremental cost per unit change in NTB.

Health and social care resource use will be collected via participant-completed questionnaires administered at baseline, 12 months and 24 months asking about the previous 12 months for care home accommodation and the previous 6 months for other health and social care resource use, using a modified version of the CSRI questionnaire [21]. Resource use will be costed using nationally published sources, including the Personal Social Services Research Unit (PSSRU) [37], NHS reference costs [38] and the British National Formulary (BNF) [39]. The cost of the intervention, applied to the intervention group only, will include the cost of training the facilitators, supervision, organising and delivering the sessions and any items purchased for the purposes of the intervention. QALYs will be calculated based on participant responses to the EQ-5D-5L captured via participant-completed questionnaires at baseline, 12 months and 24 months, using the area under the curve method and utility scores obtained from relevant UK tariffs. Costs and utilities from 12 to 24 months will be discounted at a rate of 3.5%. The mean difference in costs and QALYs between the two groups will be calculated using regression analysis adjusting for baseline, site and including clustering for facilitator in the intervention arm, with 95% confidence intervals calculated using bootstrapping.

To align the economic evaluation with the primary outcome, the primary analysis for the economic evaluation will be complete case with sensitivity analyses adjusting for predictors of missingness and multiple imputation (see section ‘Methods in analysis to handle protocol non-adherence and any statistical methods to handle missing data {20c}’). Two-part bootstrapping adjusting for baseline, site and including clustering will be used to construct cost-effectiveness acceptability curves of the probability that the intervention is cost-effective compared to the control for a range of cost-effectiveness thresholds for a QALY gained and unit change in NTB. Additional sensitivity analyses will be performed, where relevant, to assess the impact of alternative modelling assumptions on the results, including projecting 6-month resource use collected at 12 and 24 months over the full 12-month time-period between follow-ups.

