### Plans to promote participant retention and complete follow-up {18b}

Each participant is offered a £20 gift voucher after completion of each outcome assessment (baseline, 12- and 24-month follow-ups) to thank them for their time. A further £20 gift voucher is offered to each participant taking part in a process evaluation qualitative interview. If required, the outcome measures are conducted over two separate visits. Participants who indicate that they do not have time to complete follow-up have the option to complete the primary outcome only.

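### The principal 24-month cost per QALY, on its natural reading, leaves months 0-6 and 12-18 uncosted for health and social care use other than care homes, because projection to the full interval is only a sensitivity analysis

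*Protocol article*

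**What the plan says.** All of this is in the Economic evaluation section of the protocol article.

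- **Horizon:** "The economic analysis will evaluate the cost-effectiveness of the APPLE Tree intervention compared to the control over 24 months".
- **Lead analysis:** "The principal analysis will be the incremental cost per quality-adjusted life year (QALY) gained".
- **Collection points:** "Health and social care resource use will be collected via participant-completed questionnaires administered at baseline, 12 months and 24 months".
- **Recall windows:** "the previous 12 months for care home accommodation and the previous 6 months for other health and social care resource use".
- **QALYs:** area under the EQ-5D-5L utility curve through baseline, 12 and 24 months.
- **Intervention cost:** built up separately (training, supervision, delivery, purchased items) and added to the intervention arm.
- **The unasked half-years:** these appear only in the list of additional sensitivity analyses, to be run where relevant under alternative modelling assumptions, "including projecting 6-month resource use collected at 12 and 24 months over the full 12-month time-period between follow-ups".

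**The concern.** A cost per QALY needs costs and QALYs over the same period. Here the QALYs run over the whole 24 months. For everything except care home stays, the questionnaires reach back only half of the way to the previous visit. The authors noticed the gap, since they name a projection that would fill it, but they list that projection as an alternative assumption. If projecting is the alternative, the base case does not project, and the unasked half-years enter the principal result as no use at all.

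What is at stake is the headline cost per QALY and the cost-effectiveness acceptability curves built from the same costs. The first unobserved half-year matters most: the ten main sessions and the goal calls are spread over roughly the first six months, so a change in service use between arms is plausible then.

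**Working it through.** **Inputs.** From Economic evaluation: horizon 24 months; two post-randomisation questionnaires (12 and 24 months); recall 12 months for care homes and 6 months for other use; QALYs from utilities at 0, 12 and 24 months.

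**Step 1: does each component reach the stated 24 months?** Months covered = follow-up questionnaires × recall window.

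| Component | Months covered | Share of horizon |
|---|---|---|
| QALYs (curve from 0 to 24) | 24 | 100% |
| Care home accommodation | 2 × 12 = 24 | 100% |
| Intervention cost | costed directly, no recall | no gap |
| Other health and social care | 2 × 6 = 12 (months 6-12 and 18-24) | 50% |

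The 24-month horizon is reproduced for every component except the last.

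**Step 2: how much of total resource-use cost is captured?** Let s be the care home share of that cost, and assume that use is even over time. Captured share = s + 0.5 × (1 − s). The documents give no value for s, so a range is shown:

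- s = 0: 50%
- s = 0.10: 55%
- s = 0.25: 62.5%
- s = 0.50: 75%

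**Step 3: what happens to the difference between arms?** Suppose that the arms differ in other use by d in every 6-month period. The true 24-month difference is 4d and the unprojected figure is 2d. Discounting the second year at 3.5% does not change the ratio: (d + d/1.035) / (2d + 2d/1.035) = 0.5. If the difference in the unobserved months is zero, nothing is lost.

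**Step 4: illustration of the cost per QALY.** The figures are assumed, not from the documents: intervention cost £500, QALY gain 0.02, a 24-month difference D in other use spread evenly, no discounting. Unprojected = (500 + D/2) / 0.02; full period = (500 + D) / 0.02.

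| D (£) | Unprojected (£ per QALY) | Full period (£ per QALY) |
|---|---|---|
| −400 | 300/0.02 = 15,000 | 100/0.02 = 5,000 |
| 0 | 500/0.02 = 25,000 | 25,000 |
| +400 | 700/0.02 = 35,000 | 900/0.02 = 45,000 |

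The error can go either way, and it vanishes at D = 0.

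**Step 5: after the change.** With each recall projected over its interval, other use covers 2 × 12 = 24 of 24 months, half observed and half extrapolated. Care home and intervention costs do not move.

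**The case against.** The strongest reply is that the base case is never spelled out. The article does not say that months 0-6 and 12-18 are costed at zero. It lists projection among alternatives without naming the assumption that projection replaces. Resource use is also collected at baseline, so interpolation between recalls is not ruled out, and a health-economics plan may settle the matter. This stands as a limit on certainty. It does not remove the point: the article addresses the gap and puts the only method it names outside the principal analysis.

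A second reply is that the projected result is planned anyway, and that projecting has its own weakness, because it fills the intensive first half-year from a less intensive one. Both are true. Still, a conditional sensitivity analysis does not correct the principal figure, and taking the observed half-year as typical is usually easier to defend than taking the unobserved one as empty.

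A reader might infer two stronger things that the documents do not support.

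- **That costs as a whole cover only half of the horizon.** They do not. Care home accommodation is recalled over the full year at both follow-ups, and the intervention is costed separately.
- **That the complete-case base case is also an error.** The article says "To align the economic evaluation with the primary outcome, the primary analysis for the economic evaluation will be complete case", and elsewhere (Plans to promote participant retention and complete follow-up) allows follow-up with the primary outcome only. The two analysis sets may therefore differ. However, aligning can mean using the same approach to missing data as the main analyses, which rest on available data. Multiple imputation is already a planned sensitivity analysis for the economics. Which of the two leads is a trade-off, and the documents give no figures from which to size the loss.

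**Conclusion.** The point holds for health and social care use other than care home accommodation. For these items 12 of 24 months are observed. On the natural reading, the principal cost per QALY leaves the other 12 uncosted while counting 24 months of QALYs.

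The size of the error is whatever the arms differ by in months 0-6 and 12-18. That is half of the 24-month difference if the difference is constant, and zero if the arms do not differ in those months. The direction cannot be known in advance, so it would go too far to say that the principal result will be wrong or biased in a particular way. The conclusion rests on one inference, that listing projection as an alternative means the base case does not project.

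The reach is limited to a secondary objective. The primary NTB analysis is untouched.

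**What to change.** Make the principal analysis cover the full 24 months: project each 6-month recall of non-care-home use over its 12-month interval, and state this as the base case. Then report two sensitivity analyses.

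- **Unprojected:** the observed months only, labelled as covering 12 of 24 months for these items.
- **Interpolated months 0-6:** use the baseline recall as well. The baseline, unobserved and 12-month windows are centred at months −3, 3 and 9, so linear interpolation is the simple average of the baseline and 12-month recalls.

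The cost is wording in the health-economics analysis plan and a little analysis work, with no new data. The downside is small but should be stated: the base case then assumes that the observed half-year represents the unobserved one, which is least secure for months 0-6. The interpolation shows how much that assumption matters.

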## Process evaluation

We will use reflexive thematic analysis to analyse qualitative interviews [40], and NVivo 12 to manage the data. The qualitative analysis will be underpinned by a critical realist perspective, using a deductive lens based on theory-development work (see logic model in Supplementary file) and research questions about how the intervention operates to produce its outcomes, but also taking an inductive approach to identify novel findings. Researchers will systematically code transcripts into meaningful fragments and label these initial codes, discussing and resolving discrepancies [40]. Two researchers will independently code 10% of transcripts and compare coding to ensure consistency of approach. We will then develop themes responding to research questions. We will triangulate qualitative findings with fidelity ratings and 12-month quantitative outcomes, using a joint display table [41], to evaluate putative mechanisms of intervention effect. Process evaluation findings will refine our conceptual understanding of how the intervention works, building on theory developed in the APPLE Tree programme [8,9,10].

### Interim analyses {21b}

There are no plans to conduct interim analyses, as the intervention is considered low risk.

### Methods for additional analyses (e.g. subgroup analyses) {20b}

The following supportive analyses will be carried out for the primary and secondary outcomes using the same modelling approaches as described previously:Estimation of an unadjusted treatment effect.Estimation of the treatment effect adjusting for any concerning imbalances in baseline characteristics.Exploratory analysis (as sample size is calculated as sufficient for main analyses only) of whether MCI diagnosis versus SCD diagnosis (defined by Quick MCI cutpoint at baseline) moderates intervention effectiveness.

### Methods in analysis to handle protocol non-adherence and any statistical methods to handle missing data {20c}

Where there is missing outcome data, the main analyses will be based on available data, relying on an assumption that data is missing at random. Reasons for missingness will be described, and frequency (%) of subjects with missing data, by reason, will be provided for each randomised group (and for each outcome). Characteristics of participants with and without missing outcome data will be compared using logistic regression models (with missing yes/no as the outcome) to identify characteristics associated with missingness. In a sensitivity analysis, the treatment effect will be re-estimated with additional adjustment for baseline predictors of missingness. Further sensitivity analyses based on multiple imputation methods will be considered if appropriate.

### Plans to give access to the full protocol, participant-level data and statistical code {31c}

The protocol can be accessed via ISRCTN registry (ISRCTN17325135; 10.1186/ISRCTN17325135). Participant-level data and statistical code are available from the corresponding author upon reasonable request.

## Oversight and monitoring

### Composition of the coordinating centre and trial steering committee {5d}

The study is overseen by a Project Management Group (PMG) and an independent Trial Steering Committee (TSC). The PMG includes the Chief Investigator and trial manager, all co-applicants and two PPI group representatives. The group meets twice a year and sends updates to co-investigators. The PMG review recruitment figures, SAEs (serious adverse events) and substantial amendments to the protocol prior to submission to the REC. All site Principal Investigators (PIs) are kept informed of substantial amendments.

The TSC consists of an independent chair, independent statistician, two PPI representatives, Priment CTU representative, the CI, trial manager and lead statistician. The TSC will recommend any appropriate amendments/actions for the trial as necessary.

### Composition of the data monitoring committee, its role and reporting structure {21a}

The Data Monitoring Committee is combined with the TSC because the intervention is considered low risk.

### Adverse event reporting and harms {22}

Any SAEs that are classed as related and unexpected will be reported to the ethics committee and Priment CTU, according to Priment CTU standard operating procedures.

### Frequency and plans for auditing trial conduct {23}

We conduct site initiation visits prior to research sites being opened and monitor sites during the trial. We record protocol deviations and report these to the sponsor and TSC. Annual progress reports are sent to the REC.

### Plans for communicating important protocol amendments to relevant parties (e.g. trial participants, ethical committees) {25}

Where there are significant changes to our trial documentation, including the protocol, we seek an ethics amendment. The trial manager sends amendments to the sponsor for approval before submitting it to the ethics committee, notifies all researchers and research sites of the amendment submissions and outcomes and provides amended documents to sites.

### Dissemination plans {31a}

We will disseminate our findings in peer-reviewed journals and at an international conference and on the ISCTRN registry. We will present findings in local forums for health and social care professionals. Participants who have indicated on the consent form they are interested in the results will be sent a lay summary of the findings on project completion. Participants donating photographs to the archive have the option to give permission for their display in exhibitions. We plan to develop this archive into a coproduced photography exhibition to explore the lived experiences of memory loss and dementia prevention.

## Discussion

The APPLE Tree intervention is one of several large trials testing potentially scalable multidomain approaches to dementia prevention that, if successful, could make a real-world difference to dementia prevalence in whole populations. We had developed a relatively short (15 h + follow-ups) face to face group intervention prior to the pandemic, and piloted it in a form adapted for group video calls [10]. Previous remotely delivered dementia prevention interventions have been individually delivered, using internet platforms or telephone contact, and such interventions are yet to demonstrate effectiveness [42]. The HATICE trial, yet to report, is testing an interactive Internet platform, designed to encourage lifestyle changes with the remote support of a lifestyle coach to improve cardiovascular health, with cognition as a secondary outcome [43].

To our knowledge, APPLE Tree is the first group-based multidomain dementia prevention remote intervention to be trialled. In the pilot study, the group component, with peer learning and social connectedness, was valued [10]. There is a risk that an internet-delivered intervention excludes participants who are digitally excluded or not comfortable with technology, who may be at greatest need. Of the 4 million UK adults who had never used the internet in 2019, over half were aged 75 years and over [44]. We developed strategies to engage participants through working collaboratively with study partners, providing initial individual help to get online, and lending device to those without computers. These have successfully engaged many novice internet users; for example, only three of our ten pilot participants had used video calling before the intervention [10].

We are working with the NHS and NGO partners to produce an effective national implementation approach, so that if our multidomain lifestyle and behaviour intervention improves cognition, it is useful and used. We plan a pre-implementation study to explore how the intervention may be implemented successfully beyond the trial sites if it is effective.

### Trial status

The current version of the protocol is version number 5 dated 23/12/2020. The first participant was recruited on 21/10/2020. Participant recruitment is ongoing (we randomised 300 participants by November 2021) and the project recruitment is projected to end December 2022.

## Abbreviations

APPLE: Tree Active Prevention in People at risk of dementia through Lifestyle, bEhaviour change and Technology to build REsiliEnce
AUDIT-C: Alcohol Use Disorders Identification Tool
BDNF: Brain-derived neurotrophic factor
BMI: Body mass index
BNF: British National Formulary
CFT: Category fluency test
CI: Chief Investigator
COWAT: Controlled Word Association Test
CRFs: Case Report Forms
CSRI: Client Service Receipt Inventory
CTU: Clinical trials unit
EQ-5D-5L: EuroQol
GDPR: General Data Protection Regulation
GHQ-12: General Health Questionnaire
GP: General Practitioner
FINGER: Finnish Geriatric Intervention Study to Prevent Cognitive Impairment and Disability
HADS: Hospital Anxiety and Depression Scale
HBA1c: Haemoglobin A1C
HDL: High density lipoprotein
ICC: Intracluster correlation coefficient
ICH: International Conference on Harmonization
ISRCTN: International Standard Randomised Controlled Trial Number
LDL: Low-density lipoproteins
MCI: Mild cognitive impairment
MDS: Mediterranean Diet Score
NHS: National Health Service
NTB: Neuropsychological Test Battery
PI: Principal Investigator
PIS: Participant Information Sheet
PMG: Project Management Group
PPI: Public and Patient Involvement
PSQI: Pittsburgh Sleep Quality Index
PSS: Personal Social Services
PSSRU: Personal Social Services Research Unit
QALY: Quality-adjusted life year
RAVLT: Rey Auditory Verbal Learning Test
REC: Research Ethics Committee
SAE: Serious adverse event
SCD: Subjective cognitive decline
TSC: Trial Steering Committee
UCL: University College London
UEA: University of East Anglia
WMS: Wechsler Memory Scale
